### Study design

2.1

This study employs a within-subject crossover design whereby participants receive both active and sham cTBS on different days based on a randomized blinded code that is entered into the TMS machine before each session. The crossover design was chosen because of the documented heterogeneity of neuroimaging outcomes within the ASD population as well as the interindividual variability in response to cTBS and other rTMS protocols. Therefore, it was determined that a between-subject design would be less powerful in determining the acute effect of cTBS on these neuroimaging outcomes.

Participants, study staff members and all other study personnel involved in TMS administration, data collection, or data analysis are blinded to whether sham or active stimulation is delivered during each cTBS session.

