### Power analyses and sample size determination

2.3

The first aim of the study is to establish the relationship between local GABA and glutamate neurotransmitter concentrations, structural and functional network connectivity, and physiological measures of auditory/language network functioning. The estimated effect size for this aim is approximately 0.2223. This is estimated based on the literature showing a significant correlation between GABA+/Cre concentration and MEG evoked gamma power that range from 0.37-0.53 (49, 52, 56, 80). To our knowledge there is not any existing data on the correlation between the other predictor variables (DWI or functional MR connectivity) and MEG power and latency of evoked fields. However, given that both of these neuroimaging predictor variables have been shown to be aberrant in adolescents with ASD and reflect network-level structural and functional dysfunction, we predict a correlation between these neuroimaging measures and the proposed MEG measure of at least 0.15. Thus, in order to maintain 80% power with a type-I error rate of 5% and a type-II error rate of 20% we will enroll 86 ASD participants with a planned evaluable N=55 accounting for attrition.

The second aim of the study is to evaluate target engagement and the acute effects of active cTBS compared to sham cTBS on auditory/language network functioning. With planned evaluable N=55 and the minimal detectable effect (given Lehr’s equation (81)), the minimum detectible effect size is 0.38 standard deviation units, between a small (.2) and medium (.5) effect size in Cohen’s effect size taxonomy (82). We believe this is a reasonable effect size to expect given the literature. A recent study found an effect size of 0.7 on MRS GABA+/Cre concentration and 0.39 on MEG indices of sensory (visual) processing immediately following a single session of cTBS [95]. Therefore, we believe this aim is adequately powered.

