### Statistical analysis

2.5

Multiple linear regressions will be conducted to evaluate whether baseline MRS measures of local GABA and glutamate concentration, structural topography/connectivity, and/or functional activity/connectivity explain a significant proportion of the variability in MEG measures of auditory/language processing. These analyses will quantify the relationship between these measures and to what extent they may contribute to a fusion biomarker model for language processing deficits in ASD (e.g., (139)). To evaluate the effect of a single session of cTBS on MRS, fMRI, and MEG outcome measures, Factorial ANCOVAs will be conducted with time-point (pre-post) and condition (active, sham) as within-subjects variables. Other anticipated covariates in these analyses include age, gender, baseline symptom severity, and medication use. In addition to the targeted region (left pSTC), we will repeat the planned fMRI BOLD and connectivity analyses using right pSTC, left and right IFG, and a non-connected (control) cortical visual network with a temporal and frontal node to explore the spread of the effect of the cTBS from the targeted region to other structurally and functionally connected regions compared to a control network. Pearson correlation coefficients will be used for the exploratory analyses, to characterize the relationship between the neuroimaging and electrophysiological indices and baseline behavioral symptom presentation including assessments of general functioning, autism symptom severity, and auditory and language processing. As there may be intrasubject variability in these measures (independent of the cTBS intervention), we will evaluate the reliability of the baseline/pre-stimulation MEG, MRS, and fMRI outcomes by calculating the interclass correlation coefficient (Model: 2-way mixed effects, Type: mean of k measurements and Definition: absolute agreement) as a measure of test-retest reliability.

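### Repeating the time-point by condition analysis region by region gives no test of whether the cTBS effect differs between connected regions and the control network

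*Protocol article*

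**What the plan says.** The design is a crossover: "This study employs a within-subject crossover design whereby participants receive both active and sham cTBS on different days". For the cTBS outcomes, section 2.5 (Statistical analysis) names the model: "Factorial ANCOVAs will be conducted with time-point (pre-post) and condition (active, sham) as within-subjects variables". Age, gender, baseline severity and medication are listed as possible covariates.

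Beyond the stimulated left pSTC, the same section says "we will repeat the planned fMRI BOLD and connectivity analyses using right pSTC, left and right IFG, and a non-connected (control) cortical visual network", the last with a temporal and a frontal node. The purpose given is this: "explore the spread of the effect of the cTBS from the targeted region to other structurally and functionally connected regions compared to a control network".

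Section 2.5 names no region or network factor, no interaction with region and no difference contrast. The gPPI group model in section 2.4.4.4 (Task-based fMRI) adds none: it fits a separate GLM at each voxel, with subject-level identifiers as independent variables.

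Section 2.3 (Power analyses and sample size determination) sizes Aim 2 as a single active-versus-sham comparison. It gives no power statement for connected regions against the control network.

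**The concern.** The question and the method have different null hypotheses. Comparing spread with a control network has the null that the effect in the connected region equals the effect in the control network. A repeat of the two-factor ANCOVA in one region has the null that the effect in that region is zero. Running the second test four times does not produce the first.

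With only the separate results to hand, the natural reading is that spread is present where a connected region reaches p<0.05 and the control network does not. A difference in significance is not a test of a difference. That reading can suggest network specificity when the effect is the same everywhere. It can also miss real specificity when both regions pass p<0.05 with effects of different size.

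What is at stake is interpretation. The sham condition removes whatever active and sham sessions share. It does not show whether a remaining active-minus-sham difference is confined to the language network, and the comparison with the control network bears on that. The Discussion would use increased language-network connectivity to argue that multiple sessions might help, through links from left pSTC to inferior frontal and right pSTC regions.

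**Working it through.** **Inputs from section 2.3.** "With planned evaluable N=55 and the minimal detectable effect"; a "type-I error rate of 5% and a type-II error rate of 20"%; "the minimum detectible effect size is 0.38 standard deviation units". The literature cited for Aim 2 is "an effect size of 0.7 on MRS GABA+/Cre concentration and 0.39 on MEG indices of sensory (visual) processing". No effect size is given for fMRI.

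**Reproducing the plan's figure.** Lehr's equation in paired form gives d = √(8/55) = 0.381. The normal formula gives (1.960 + 0.842)/√55 = 0.378. Both round to 0.38. The two-group form, √(16/55) = 0.539, does not. The stated 0.38 is therefore a paired figure for one test in one region.

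**Set-up.** For each participant and region, take the double difference: (post minus pre under active) minus (post minus pre under sham). Without covariates, the time-point by condition interaction is a one-sample t-test on it. *Assumptions, because the article gives none of these for fMRI:* the same true effect d in every region, in SDs of the double difference; a common between-region correlation rho; two-sided 5% tests without correction.

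**Independent regions (noncentral t, n = 55).** With power p, one given connected region is significant and the control is not with probability p(1−p). For at least one of three connected regions it is [1−(1−p)³](1−p).

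- d = 0.38: p = 0.790. One region: 0.790 × 0.210 = 0.166. Any of three: (1 − 0.210³) × 0.210 = 0.208.
- d = 0.20: p = 0.308. One region 0.213; any of three 0.463.
- d = 0.50: p = 0.954. One region 0.044; any of three 0.046.
- d = 0.70: p = 0.999. About 0.001 for either.

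**Correlated regions (simulation, 16,000 trials per cell).** Each cell gives one given region / any of three.

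| rho | d = 0.20 | d = 0.38 | d = 0.50 |
|---|---|---|---|
| 0 | 21.7% / 46.6% | 16.6% / 21.1% | 4.2% / 4.4% |
| 0.3 | 17.8% / 36.4% | 14.1% / 19.4% | 4.0% / 4.6% |
| 0.5 | 15.1% / 30.3% | 11.8% / 17.5% | 3.5% / 4.5% |
| 0.7 | 10.9% / 22.0% | 8.8% / 13.9% | 3.0% / 4.0% |
| 0.9 | 6.5% / 12.4% | 5.1% / 8.8% | 1.6% / 2.6% |

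**Direct contrast on the same data.** The t-test of one connected region minus control rejects in 4.8% to 5.4% of trials in every cell simulated, so about 2.5% in the direction of more effect than control.

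**Sensitivity of the direct contrast.** The SD of a one-region-minus-control difference is √(2(1−rho)). Its minimum detectable difference at 80% power is therefore 0.378 × √(2(1−rho)): 0.53 at rho 0, 0.45 at 0.3, 0.38 at 0.5, 0.29 at 0.7 and 0.17 at 0.9. It matches the single-region test at rho = 0.5.

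**The case against.** The strongest reply is that the article never says spread will be declared from significance in one place and non-significance in another, nor that a null control result will be taken as no effect. It produces regional results and announces a comparison; the form of that comparison could sit in an unseen analysis plan. This stands in part. A reader might infer that the plan commits to the faulty rule; the text does not support that, and the rates above are conditional on it. What remains is that the article does state a method for a comparative purpose, and the stated method contains no test of the comparison.

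A reader might also infer that the control network is the plan's only protection against a non-specific effect. It is not. Section 2.4.3 describes an active/placebo coil with visually identical sides, balanced orders, and a blinding guess with loudness, pain and twitch ratings after each session. Section 2.4.4.4 censors high-motion volumes, section 2.4.4.5 includes outlier detection and denoising, and the Discussion adds mock-scanner practice. Drift or arousal common to active and sham sessions cancels in the time-point by condition interaction.

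Three limits on size also stand.

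- A shared global influence could make regional effects strongly correlated, which pulls the rates towards the bottom rows of the table.
- Setting the any-of-three rate against one 5% contrast would overstate the excess, because part of it is multiplicity. With no effect anywhere and independent regions, the any-of-three pattern already occurs with probability (1 − 0.95³) × 0.95 = 0.135. The one-region figures are the fairer comparison.
- Section 2.4.4.4 uses a voxel threshold of p<0.001 with a cluster-level FDR for gPPI, so 5% single-test rates do not apply there.

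Finally, the analysis is described as exploring, and the hypotheses under Anticipated results concern active versus sham. That lowers the severity, but it does not make a one-region test answer a two-region question.

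**Conclusion.** The concern holds in a limited form. Section 2.5 poses a connected-versus-control question and answers it with separate regional tests, none of which tests that difference.

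If spread were read from the pattern of significance, an effect equal in all regions would look specific to one given connected region in about 17% to 5% of trials at the plan's own 0.38 SD, and to at least one of three in about 21% to 9%, as rho goes from 0 to 0.9. Rates are higher at 0.20 SD; at 0.5 SD or more they are 5% or less. They rest on N = 55, uncorrected two-sided 5% tests, and assumed effect sizes and correlations. The 0.38 SD is a generic detectable effect, not one expected in visual cortex.

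A reader might go further and infer that Aim 2 as a whole is compromised. The documents do not support that: the active-versus-sham test in left pSTC does not depend on this comparison. Severity is modest. The change is worth making because it is nearly free.

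**What to change.** For the ROI-level fMRI outcomes, fit one model per outcome with region or network as a third within-subject factor. Name the connected-versus-control by time-point by condition contrast, with its estimate and 95% CI, as the basis for any statement on spread or network specificity. Keep the separate regional results as description, and state that a non-significant control result will not be reported as absence of effect. If each connected region is contrasted with the control in turn, say how the three contrasts are handled together.

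The cost is a few lines of analysis-plan wording and one model term, with no new data. The article describes main-phase enrolment as under way, so this should be fixed before the treatment codes are opened. The downside is that a one-region contrast has less power than a single-region test when the between-region correlation is below about 0.5 (detectable difference 0.53 SD at rho 0, against 0.38), so fewer specificity claims may be made.

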## Abstract

It has been suggested that aberrant excitation/inhibition (E/I) balance and dysfunctional structure and function of relevant brain networks may underlie the symptoms of autism spectrum disorder (ASD). However, the nomological network linking these constructs to quantifiable measures and mechanistically relating these constructs to behavioral symptoms of ASD is lacking. Herein we describe a within-subject, controlled, proof-of-mechanism study investigating the pathophysiology of auditory/language processing in adolescents with ASD. We utilize neurophysiological and neuroimaging techniques including magnetic resonance spectroscopy (MRS), diffusion-weighted imaging (DWI), functional magnetic resonance imaging (fMRI), and magnetoencephalography (MEG) metrics of language network structure and function. Additionally, we apply a single, individually targeted session of continuous theta burst stimulation (cTBS) as an experimental probe of the impact of perturbation of the system on these neurophysiological and neuroimaging outcomes. MRS, fMRI, and MEG measures are evaluated at baseline and immediately prior to and following cTBS over the posterior superior temporal cortex (pSTC), a region involved in auditory and language processing deficits in ASD. Also, behavioral measures of ASD and language processing and DWI measures of auditory/language network structures are obtained at baseline to characterize the relationship between the neuroimaging and neurophysiological measures and baseline symptom presentation. We hypothesize that local gamma-aminobutyric acid (GABA) and glutamate concentrations (measured with MRS), and structural and functional activity and network connectivity (measured with DWI and fMRI), will significantly predict MEG indices of auditory/language processing and behavioral deficits in ASD. Furthermore, a single session of cTBS over left pSTC is hypothesized to lead to significant, acute changes in local glutamate and GABA concentration, functional activity and network connectivity, and MEG indices of auditory/language processing. We have completed the pilot phase of the study (n=20 Healthy Volunteer adults) and have begun enrollment for the main phase with adolescents with ASD (n=86; age 14-17). If successful, this study will establish a nomological network linking local E/I balance measures to functional and structural connectivity within relevant brain networks, ultimately connecting them to ASD symptoms. Furthermore, this study will inform future therapeutic trials using cTBS to treat the symptoms of ASD.

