	AD	1.24 ± 0.03 (n=19)

GABA and Glutamate concentrations are measured over creatine. The MRS voxel was centered on the individualized cTBS target as defined by the peak bold activation to the ADDT task. Voxels were 2.5 cm cubed, thus the value represents relative concentrations of metabolites within the posterior superior temporal cortex.

Mean and standard deviation values for Evoked Gamma Power and FA are dimensionless.

Mean and standard deviation values for MD, RD, and AD are measured in 10^-3^ mm^2^/s.

Sample sizes varied based on data quality and visit completion.

FA, Fractional Anisotropy; MD, Mean Diffusivity; RD, Radial Diffusivity; AD, Axial Diffusivity.

For the main phase, ASD individuals must meet the following inclusion criteria: (1) Age 14-17, (2) Community diagnosis of ASD based on DSM-IV or DSM-5 criteria, (3) FSIQ > 70, (4) Right-handed, and (5) Normal hearing. In addition to the exclusion criteria listed above for the pilot phase of the study, in the main phase individuals with known genetic disorders associated with the ASD diagnosis or that in the opinion of the investigator may increase the risk to the participant or compromise the integrity of the data will also be excluded. In the main phase of the study, we will acquire the same baseline assessments as in the pilot phase as well as additional behavioral/neuropsychological assessments related to their ASD diagnosis and their receptive and expressive language skills. Participants will also complete an audiometric evaluation to confirm that they have normal hearing. To reduce burden to the participant these baseline visits can be further divided. Additionally, each ASD participant will receive both active and sham cTBS on two separate sessions, combined with MRI and combined with MEG for a total of four imaging/cTBS visits instead of the two in the pilot phase.

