We also perform a psychophysiological interaction analysis with the CONN toolbox to study the functional connectivity changes, using the same seed regions. For each pair of seed and target areas, a generalized psychophysiological interaction model (gPPI (127, 128)) is defined with seed BOLD signals as physiological factors, boxcar signals characterizing each individual task condition convolved with an SPM canonical hemodynamic response function as psychological factors, and the product of the two as psychophysiological interaction terms. Functional connectivity changes across conditions are characterized by the Fisher-transformed semi partial correlation coefficient of the psychophysiological interaction terms in each model. Finally, group-level analyses are performed using a General Linear Model (GLM (129)). For each individual voxel a separate GLM is estimated, with first-level connectivity measures at this voxel as dependent variables (one independent sample per subject and one measurement per experimental condition), and groups or other subject-level identifiers as independent variables. Voxel-level hypotheses are evaluated using multivariate parametric statistics with random-effects across subjects and sample covariance estimation across multiple measurements. Inferences are performed at the level of individual clusters (groups of contiguous voxels). Cluster-level inferences are based on parametric statistics from Gaussian Random Field theory (130, 131). Results are thresholded using a combination of a cluster-forming p < 0.001 voxel-level threshold, and a familywise corrected p-FDR < 0.05 cluster-size threshold (132).

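### Test-retest reliability is specified as the ICC for a mean of k scans, although no averaging of scans is described, so the figure will overstate the reliability of a single scan

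*Protocol article*

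**What the plan says.** Section 2.5 (Statistical analysis) gives the motive for the reliability analysis: "As there may be intrasubject variability in these measures (independent of the cTBS intervention". The analysis covers the MEG, MRS and fMRI measures taken at baseline and before stimulation. The section then fixes all three attributes of the coefficient: "Model: 2-way mixed effects, Type: mean of k measurements and Definition: absolute agreement) as a measure of test-retest reliability". It does not give k, list the scans that enter, or mention a single-measurement version.

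The analyses that use these measures are described as follows.

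- **Aim 1 (section 2.5):** "Multiple linear regressions will be conducted to evaluate whether baseline MRS measures of local GABA and glutamate concentration", together with structural and functional measures, explain variability in the MEG measures.
- **Aim 2 (section 2.5):** "Factorial ANCOVAs will be conducted with time-point (pre-post) and condition (active, sham) as within-subjects variables".
- **Exploratory (section 2.5):** Pearson correlations between the imaging indices and baseline symptoms.
- **Task connectivity group model (section 2.4.4.4):** "one independent sample per subject and one measurement per experimental condition".

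On the number of occasions, the Abstract says that "MRS, fMRI, and MEG measures are evaluated at baseline and immediately prior to and following cTBS", and section 2.2 says that "each ASD participant will receive both active and sham cTBS on two separate sessions, combined with MRI and combined with MEG".

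**The concern.** An ICC for the mean of k measurements answers this question: if each participant were scanned k times and the values averaged, how reliable would that average be? Occasion-to-occasion noise has then already been divided by k. The sentence in section 2.5 asks something else, namely how far a person's value moves between occasions without active stimulation. The single-measurement form of the same two-way, absolute-agreement ICC answers that.

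The choice is written out in the article, so this is not a detail left to an analysis plan that is not shown. At stake is a published reliability figure that looks better than the scans as used. A reader who relies on it to judge how far measurement noise has weakened the Aim 1 associations, or to plan a study with one scan per participant, would be too optimistic.

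**Working it through.** **Inputs**

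- Coefficient: two-way mixed, absolute agreement, mean of k, written ICC(A,k) (section 2.5).
- k: not stated. The Abstract and section 2.2 imply three stimulation-free occasions per modality in the main phase (baseline, pre-active, pre-sham), or two if only the cTBS visits are used. Both values are carried below as assumptions.
- True single-scan ICC: not given. Assumed range 0.30 to 0.90.
- n = 55, the planned evaluable number (section 2.3), used only in the simulation.

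The article states no ICC value, so there is no figure of its own to reproduce.

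**Formulas.** With mean squares for participants (MSR), occasions (MSC) and error (MSE):

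- ICC(A,1) = (MSR − MSE) / [MSR + (k − 1)MSE + (k/n)(MSC − MSE)]
- ICC(A,k) = (MSR − MSE) / [MSR + (MSC − MSE)/n]

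The two are linked exactly by Spearman-Brown: ICC(A,k) = k·ICC(A,1) / [1 + (k − 1)·ICC(A,1)].

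**Numbers in**

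| Single-scan ICC | Reported if k = 2 | Reported if k = 3 |
|---|---|---|
| 0.30 | 0.60/1.30 = 0.46 | 0.90/1.60 = 0.56 |
| 0.40 | 0.80/1.40 = 0.57 | 1.20/1.80 = 0.67 |
| 0.50 | 1.00/1.50 = 0.67 | 1.50/2.00 = 0.75 |
| 0.60 | 1.20/1.60 = 0.75 | 1.80/2.20 = 0.82 |
| 0.70 | 1.40/1.70 = 0.82 | 2.10/2.40 = 0.88 |
| 0.90 | 1.80/1.90 = 0.95 | 2.70/2.80 = 0.96 |

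For k > 1 the specified ICC is higher whenever the single-scan ICC lies between 0 and 1.

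**In reverse.** ICC(A,1) = R / [k − (k − 1)R]. A reported R = 0.75 means 0.75/1.25 = 0.60 with k = 2, or 0.75/1.50 = 0.50 with k = 3.

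**Simulation check.** With n = 55, 4,000 replicates and no systematic visit shift, a true single-scan ICC of 0.50 gave mean estimates of 0.49 for ICC(A,1) and 0.74 for ICC(A,k) at k = 3 (0.50 and 0.66 at k = 2). The identity held to rounding error in every replicate.

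**What it does to a judgement on attenuation.** Noise in one variable multiplies a true correlation by the square root of that variable's reliability. If the single-scan ICC is 0.50, the factor is √0.50 = 0.71. Reading the k = 3 figure of 0.75 as single-scan reliability suggests √0.75 = 0.87.

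**Which analyses use single scans**

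- Aim 2: explicit. Pre and post enter separately within active and sham, and averaging the pre-stimulation scans over visits would remove the distinction that the model needs.
- Task connectivity model: its wording fits single measurements.
- Aim 1 and the correlations: inferred. They refer to baseline values, and section 2.2 describes baseline visits as dividing the modalities between visits, not as repeating a modality. No averaging step is described.

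**The case against.** The strongest reply has four parts.

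1. **Aim 1 might pool scans.** Section 2.5 groups baseline and pre-stimulation scans together, and a condensed article need not say whether they are averaged for Aim 1. If they are, ICC(A,k) is the right coefficient for that analysis. This stands as a limit: a reader might infer that every planned analysis uses single scans, but the article shows this clearly only for Aim 2. Pooling in Aim 1 would still leave Aim 2 unmatched.

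2. **k = 3 is not established.** This stands. Section 2.4.4.1 lists the MEG datasets as baseline plus post-stimulation, which does not sit easily with the Abstract, so the set of scans entering the ICC is unclear. The size must be shown for both k = 2 and k = 3.

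3. **Aim 2 does not depend on the ICC.** A reader might infer that an inflated ICC would cause null Aim 2 results to be misread. That does not follow. With independent scan errors of variance σ², the contrast (post − pre, active) − (post − pre, sham) carries error variance 4σ², and stable between-person differences cancel. The ICC mixes σ² with between-person variance: a low single-scan ICC can go with good Aim 2 precision in a homogeneous sample, and a high one with poor precision in a heterogeneous sample. The useful figure for Aim 2 is the within-subject SD.

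4. **Little depends on the coefficient.** The article sets no reliability cut-off, does not use the ICC in section 2.3, and does not cite it in the Discussion when it covers null results. The form is openly labelled, and ICC(A,1) can be recovered once k is reported. This limits the importance of the point, but it does not make the coefficient fit its stated purpose.

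**Conclusion.** The point holds in a limited form. Section 2.5 commits to a coefficient that describes an average over occasions, while its own rationale is variability between occasions and no averaging is described. The direction of the error is certain for a single-scan ICC between 0 and 1. In absolute terms the overstatement is 0.16 (k = 2) or 0.26 (k = 3) at a single-scan ICC of 0.30, 0.17 or 0.25 at 0.50, and 0.15 or 0.22 at 0.60; it shrinks towards the top of the scale. These sizes rest on assumed values of k and of the true ICC.

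The consequence is an over-favourable descriptive figure, relevant mainly to attenuation in Aim 1 and the correlations and to the planning of later studies. A reader might go further and infer that unreliable measures would be declared reliable, or that the power or tests of either aim are affected. The article does not support either inference: it has no cut-off, and no test, sample size or decision uses the ICC.

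**What to change.** In section 2.5:

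- Change the type to single measurement, keeping the two-way model and absolute agreement, and report ICC(A,1) with a 95% confidence interval.
- State k and which scans enter for each modality (baseline, pre-active, pre-sham).
- Report the mean-of-k ICC only alongside an analysis that actually uses the k-scan average. If Aim 1 is meant to use that average, say so.
- For Aim 2, also report the within-subject SD (standard error of measurement).

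The cost is a few words in section 2.5 and a few extra lines of output. No new data are needed, and no planned test changes.
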